### 2.8. Safety and Adverse Event

The following tests will be performed to assess the safety at screening and 8 weeks: white blood cell, red blood cell, hemoglobin, hematocrit, platelet, aspartate aminotransferase, alanine aminotransferase, gamma-glutamyl transpeptidase, blood urea nitrogen, creatinine, and erythrocyte sedimentation rate. These tests will enable the investigators to exclude subjects with serious diseases before randomization and to verify the safety of the 8-week administration of YGJT in FD patients.

Adverse events (AEs) including serious AEs will be reported and recorded in detail during the entire study. An AE is any untoward medical occurrence that will not necessarily have a causal relationship with an investigational drug. Therefore, an AE can be any unfavorable and unintended sign (including an abnormal laboratory finding), symptom, or disease temporally associated with the use of the investigational drug, whether or not related to those. If any AEs occur, the appropriate treatment will be provided to the subject immediately. A serious AE will be defined as an event resulting in death, a life-threatening event, an illness requiring hospitalization, or persistent or significant disability. All of the serious AEs will be promptly reported to the institutional review board and the principal investigator within 24 hours.

### 2.9. Sample Size Calculation

The formula for estimating the sample size is as follows:(1)N=nt+ncnt,the number of treatment group;nc,the number of control groupnc=12nt=Zα/2+Zβ2σ2λ+1/λμc−μt2.

A previous study demonstrated 1.57 points of improvement (*μ*_*c*_ − *μ*_*t*_ = *δ*) in the TDS scale for FD after 4 weeks of YGJT treatment compared with that after the placebo treatment [17]. The study indicated a mean standard deviation (SD = *σ*) of 2.148. In the present study, the ratio (*λ*) of the treatment group to the control group will be 2 : 1 (*λ* = 2). With a power (1 − *β*) of 80% and a significance level (*α*) of 5%, assuming *δ* = 1.57 and *σ* = 2.148, a sample size of *n*_*t*_ = 44 and *n*_*c*_ = 22 subjects will be required. Considering an assumed dropout rate of 30%, a total of 96 subjects will be needed in the current study.

### 2.10. Statistical Analysis

An independent statistician who is blinded to group allocation will conduct statistical analysis. All data will be presented as mean ± standard deviation or number (%). Baseline characteristics of the subjects will be analyzed using chi-squared test or Fisher's exact test for categorical variables and analysis of variance (ANOVA) for continuous variables. For the efficacy analysis, two-way ANOVA will be used to compare the changes in scores of each outcome for 8 weeks between the intervention groups or the facial shape types. For the safety analysis, the chi-squared test or Fisher's exact test will be used. Both* intention-to-treat* (ITT) and* per-protocol* (PP) analyses will be performed in the current trial, and the primary analysis will be based on the ITT analysis. For the ITT analysis, a full analysis set will be used, and all subjects randomly allocated to one of the two groups, have taken at least one dose of the investigational drugs, and have reported once at least the primary outcome after the baseline will be included. Missing data will be adjusted using the last observation carried forward method. For the PP analysis, all subjects who have completed the study and have complied well with the study protocol without major protocol violations will be included. The subjects with <70% compliance will be excluded from the PP analysis. For the safety analysis, all subjects who have taken at least one dose of the investigational drugs will be included. SPSS 21.0 (IBM SPSS Statistics, New York, USA) will be used for all statistical analyses. A* P* value < .05 will be considered statistically significant.

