### 2.4. Randomization, Allocation Concealment, and Blinding

Randomization will be separately performed at each center by an independent statistician. The subjects will be randomly assigned to the treatment or control group in a 2 : 1 ratio using block randomization method. This ratio is chosen because it will be more ethical to assign twice the number of subjects who will take placebo to the treatment group than to allocate equal number of subjects to each group [17]. Random numbers will be generated using the PROC PLAN of SAS 9.4 (SAS Institute Inc., Cary, NC, USA) by the independent statistician. The statistician will arrange the random numbers of each center in the two types (bladder body, gallbladder body) of facial shape and send the allocation lists to an independent staff. The staff will be in charge of the 3-FSDS program operation and know the type of facial shape of each subject.

When a subject passes the screening and eligibility test, his/her face image will be taken and stored using the 3-FSDS. Subsequently, the image will be sent to the independent staff operating the 3-FSDS program; the type of facial shape will be classified by 3-dimensional facial measurement using the 3-FSDS program. After the type is determined, the staff will immediately inform an investigator of the center through e-mail whether the subject will be included in the trial considering the fixed number of subjects for each type (24 bladder body, 24 gallbladder body at each center). If the subject is included in the trial, the staff will send a random number in the allocation list arranged in sequential order in each type to the investigator of the center through e-mail. Additionally, if the fixed number of subjects of each type is already full, the staff will notify the investigator that the new subject will be excluded from the trial.

The subjects, investigators, clinical research coordinator (CRC), and clinical pharmacist will be blinded to the random allocation of the trial. Only the independent statistician will be associated with the randomization. The independent staff operating the 3-FSDS program will know only the type of facial shape not the group allocation of each subject.

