### 2.7. Outcome Measurements

#### 2.7.1. Primary Outcome

*Total Dyspepsia Symptom Scale (TDS Scale)*. The TDS scale comprises 8 items (postprandial fullness and bloating, early satiety, epigastric pain, epigastric burning, nausea, vomiting, belching, and other symptoms), with a 4-point Likert scale [17, 32]. The TDS score is the total score of 8 items. This scale will be assessed at baseline, 4 weeks, and 8 weeks.

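### The efficacy model, a two-way ANOVA on change scores, omits the baseline score and centre: the comparison stays unbiased, but precision of uncertain size is given away

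*Protocol article*

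**What the plan says.** Section 2.10 of the protocol article names the efficacy model outright: "two-way ANOVA will be used to compare the changes in scores of each outcome for 8 weeks". The factors it then lists are treatment group and facial type. No baseline covariate and no centre term is named.

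Both missing variables are in hand:

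- **Baseline.** Section 2.7.1 says of the primary outcome, the total dyspepsia symptom (TDS) score: "This scale will be assessed at baseline, 4 weeks, and 8 weeks". Section 2.7.2 measures the other scores at the same three times.
- **Centre.** Section 2.4 states: "Randomization will be separately performed at each center by an independent statistician". The statistician will also "arrange the random numbers of each center in the two types (bladder body, gallbladder body) of facial shape", with a fixed quota of "24 bladder body, 24 gallbladder body at each center".

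Randomisation is thus stratified by centre and facial type. Of these two strata, facial type is in the model and centre is not.

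**The concern.** A change score subtracts the whole of the baseline value, which amounts to fixing the baseline slope at 1. If the true slope is below 1, the subtraction over-corrects: part of any chance baseline difference between arms passes into the estimate and adds to its variance. Such differences are plausible here. At 2:1, each centre-by-type cell of 24 holds 8 placebo patients, so there are 4 × 8 = 32 placebo patients in all and 16 per type.

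Centre raises a similar but smaller issue. When allocation is balanced within centre and the analysis ignores centre, between-centre variation stays in the error term.

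At stake are the width of the interval for the primary contrast and the power of the comparison between facial types, on which section 3 rests the judgement about the facial diagnostic device.

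**Working it through.** **Inputs from the article.** From section 2.9: difference 1.57 TDS points ("A previous study demonstrated 1.57 points of improvement", a 4-week result), SD 2.148, 80% power, 5% significance with Zα/2, ratio 2:1, dropout 30%. The section does not say whether 2.148 is the SD of change or of the score.

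**Inputs assumed.** The correlation ρ between baseline and week-8 TDS (0.3, 0.5, 0.7), and k = baseline SD / week-8 SD (1, 0.8, 0.7). The article gives neither.

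**1. The plan's own figure.** n_c = (1 + 1/2) × [2.148 × (1.960 + 0.842) / 1.57]² = 22.04. The article takes 22, hence n_t = 44 and 66 evaluable. Dropout: 66/0.7 = 94.3, so 95, taken to 96, which fills four cells of 24. The stated sample size reproduces. Power at 44/22 is 79.9% by the normal approximation and 78.7% by the noncentral t, which is used below (64 df).

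**2. Variance ratio.** Let the week-8 SD be s and the baseline SD ks.

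- Change score: variance s²(1 + k² − 2ρk).
- ANCOVA residual: s²(1 − ρ²).
- Ratio: (1 − ρ²) / (1 + k² − 2ρk). At k = 1 this is (1 + ρ)/2.

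The change-score variance minus the ANCOVA variance is s²(k − ρ)², which is never negative. Apart from the degree of freedom spent on the slope, ANCOVA cannot do worse. The two coincide when ρ = k, that is, when the slope ρ/k equals 1.

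**3. Power at 44/22 with baseline in the model**, taking 2.148 as the SD of change and 2.148 × √ratio as the residual SD. The comparator is 78.7%.

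| k | ρ = 0.3: ratio, power | ρ = 0.5: ratio, power | ρ = 0.7: ratio, power |
|---|---|---|---|
| 1.0 | 0.65, 92.8% | 0.75, 88.9% | 0.85, 84.9% |
| 0.8 | 0.78, 87.5% | 0.89, 83.1% | 0.98, 79.5% |
| 0.7 | 0.85, 84.8% | 0.95, 80.8% | 1.00, 78.7% |

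Using 60 df, for the full model with six parameters, changes each power by about 0.1 point or less.

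**4. If 2.148 is the SD of the score instead (k = 1).** The change SD is 2.148 × √(2(1 − ρ)) and the ANCOVA SD is 2.148 × √(1 − ρ²). By the normal approximation, power at 44/22 for change score and ANCOVA is 65.8% and 83.5% at ρ = 0.3, 79.9% and 89.8% at ρ = 0.5, and 95.1% and 97.5% at ρ = 0.7.

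**5. Centre.** Two equal centres that differ by an assumed 1 point add (1/2)² = 0.25 to the variance. Against 2.148² = 4.61 that is 5.4%. Removing it moves power from 78.7% to 80.9%. The 1-point difference is only an illustration and has no source in the article.

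**6. Facial-type interaction.** With 22/11 per type and an assumed interaction as large as the whole planned effect (1.57), the standard error is SD × √[2(1/22 + 1/11)]. Power is 28% under the planned model and 40%, 36% or 32% with baseline at k = 1 and ρ = 0.3, 0.5 or 0.7. It stays low, but the precision is worth having.

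**The case against.** The strongest reply is that this is a preference about efficiency and not an error. Under randomisation a change-score comparison is unbiased, and its standard error already reflects chance baseline imbalance. That stands. A reader might infer that the planned test is invalid, that its estimate is biased, or that the sample size in 2.9 is wrong. The article supports none of these: step 1 reproduces the sample size, and leaving out a stratum such as centre makes the test mildly conservative.

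The second reply is that the size cannot be read from the article. This also stands. It would be tempting to say that adjustment is worth a third more patients (1/0.75 = 1.33), but that is one cell of the table, at ρ = 0.5 with equal SDs. Section 2.2.1 admits only patients above 40 points on the VAS. Such a restriction could make the baseline spread smaller than the week-8 spread, and at k = 0.7 and ρ = 0.7 the gain is nil.

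Third, 96 patients are enrolled, and the full analysis set with last observation carried forward keeps anyone with one post-baseline TDS score. With no loss at all, at 64/32, the planned model already has 92% power on the article's inputs. The loss for the primary contrast may therefore be smaller than the 44/22 figures suggest.

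Finally, covariates are often left to the analysis plan, which is not shown. This carries less weight, because section 2.10 names the model and its two factors. Adding terms later would change a stated analysis rather than complete one.

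**Conclusion.** The point holds as lost efficiency of uncertain size. Section 2.10 leaves out a covariate that the trial already measures and a factor within which it randomises.

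Taking 2.148 as the SD of change, adjusting for baseline at 44/22 adds about 6 to 14 percentage points of power when the SDs are equal, about 1 to 9 points at k = 0.8, and 0 to about 6 points at k = 0.7, for ρ between 0.3 and 0.7. The direction is secure, because the ANCOVA residual variance never exceeds that of the change score. The amount rests on ρ, k and the meaning of 2.148, none of which the article gives. Centre contributes little unless the centres differ clearly. This is a free improvement and not a correction of an invalid analysis.

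**What to change.** In section 2.10, make the primary analysis of each score an ANCOVA of week-8 change on treatment, facial type, treatment × facial type, centre and the baseline value of the same score. Report adjusted differences with 95% confidence intervals. Keep the unadjusted two-way ANOVA as a sensitivity analysis.

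The cost is one sentence. Every variable is already collected, no further patients are needed, and the sample size can stay as it is. The change should be fixed before unblinding, so that the decision to adjust does not depend on the baseline comparisons that 2.10 also plans.

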## Abstract

*Introduction*. Functional dyspepsia (FD), a common upper gastrointestinal disease, is difficult to manage because of the limitations of current conventional treatments. Yukgunja-tang (YGJT) is widely used to treat FD in clinical practice in Korea, Japan, and China. However, YGJT significantly improves few symptoms of FD. In Korean medicine, FD is a well-known functional gastric disease that shows difference in the effect of herbal medicine depending on constitution or type of Korean medicine diagnosis. This study aims to investigate the efficacy of YGJT on FD patients classified by 3-dimensional facial measurement using a 3-dimensional facial shape diagnostic system (3-FSDS).* Methods*. A placebo-controlled, double-blind, randomized, two-center trial will be performed to evaluate the efficacy of YGJT on FD patients. Eligible subjects will be initially classified as two types by 3-dimensional facial measurement using the 3-FSDS. Ninety-six subjects (48 subjects per each type) will be enrolled. These subjects will be randomly allocated into treatment or control groups in a 2 : 1 ratio. YGJT or placebo will be administered to each group during the 8-week treatment period. The primary outcome is total dyspepsia symptom scale, and the secondary outcomes include single dyspepsia symptom scale, proportion of responders with adequate symptom relief, visual analog scale, Nepean dyspepsia index-Korean version, functional dyspepsia-related quality of life, and spleen qi deficiency questionnaire.* Discussion*. This is the first randomized controlled trial to assess the efficacy of the YGJT on FD patients classified by 3-dimensional facial measurement. We will compare the treatment effect of the YGJT on FD patients classified as two types using the 3-FSDS. The results of this trial will help the FD patients improve the symptoms and quality of life effectively and provide objective evidence for prescribing the YGJT to FD patients in clinical practice.* Trial Registration*. This trial is registered with Clinical Research Information Service Identifier: KCT0001920, 15 May, 2016.

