## 3. Discussion

This paper describes the protocol of a trial to investigate the efficacy of YGJT on FD patients classified by 3-dimensional facial measurement. This study is the first to explore the difference of the treatment effect of YGJT on FD patients classified as different types of facial shape using the 3-FSDS.

YGJT has widely been used to treat dyspeptic symptom of upper gastrointestinal diseases including FD in clinical practice in Korea, Japan, and China [8–10, 12]. A few animal and human studies have demonstrated that YGJT is effective on symptoms of FD. However, YGJT is reported to significantly improve only some symptoms of FD in clinical trials. Suzuki et al. [18] conducted a multicenter, double-blind, randomized, placebo-controlled, parallel-group trial to assess the efficacy and safety of YGJT on 247 FD patients. They showed that epigastric pain, an FD symptom, is significantly reduced by administration of YGJT. However, no significant differences were found on the proportion of patients with relief of other symptoms, such as epigastric burning, postprandial fullness, and early satiation, between the YGJT and placebo groups. In addition, a clinical trial with FD patients performed by Kusunoki et al. [20] reported that although the total score of the gastrointestinal symptom rating scale decreases after treatment with YGJT, the differences are not statistically significant. This finding may be caused by the treatment of FD, which is affected by specific constitution and type of Korean medicine diagnosis of patients. Differences of treatment effect of identical herbal medicine between FD patients with different constitutions or diagnosis types are possible. In traditional Korean medicine, particular facial characteristics have been believed to refer to assessable information related to an individual's diseases, and Hyungsang medicine has been developed as a constitutional medicine based on a Korean classical medicine literature, Donguibogam. According to the theory of Hyungsang medicine, the bladder body type has deficient qi and excessive dampness; on the other hand, the gallbladder body type has deficient Yin-blood and excessive heat. Therefore, YGJT is considered as a herbal medicine which is more effective to the bladder body type [22, 41]. Accordingly, we will examine the efficacy of YGJT on FD patients classified as bladder or gallbladder body by 3-dimensional facial measurement using the 3-FSDS.

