In addition, we will evaluate the usefulness of the 3-FSDS comparing the treatment effect of YGJT, which is more effective on patients classified as the bladder than the gallbladder body in the theory of Hyungsang medicine, for FD patients classified as different facial shape types using the 3-FSDS. As mentioned above, the 3-FSDS is a diagnostic device developed to overcome the limitations of the existing methods for the facial shape diagnosis. If the symptoms of FD in this trial more significantly improve patients classified using the 3-FSDS as the bladder than the gallbladder body, then the 3-FSDS can be used to classify the different types of facial shape by 3-dimensional facial measurement.

The results of the current study are expected to demonstrate whether YGJT administration shows difference of treatment effect on FD patients depending on the facial shape types classified as bladder or gallbladder body using the 3-FSDS. If the efficacy of YGJT on FD patients classified as specific type is proven in this trial, their dyspeptic symptoms and quality of life will improve more effectively. The objective evidence for prescribing YGJT to FD patients diagnosed as specific facial shape type will also be provided with more confidence in clinical practice. In addition, if the usefulness of the 3-FSDS is verified, the 3-FSDS will be widely used in clinical practice as a device to diagnose facial shape type by 3-dimensional facial measurement more objectively. Furthermore, more objective diagnosis will aid in achieving a more effective treatment.

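### The treatment-by-type interaction is not named as the test of the facial-type question, and the stated criterion for the 3-FSDS makes no reference to placebo

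*Protocol article*

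**What the plan says.** The aim is effect modification. The Abstract states: "We will compare the treatment effect of the YGJT on FD patients classified as two types using the 3-FSDS". The Discussion repeats it: "This study is the first to explore the difference of the treatment effect of YGJT on FD patients classified as different types of facial shape". Section 1 adds verification of the usefulness of the 3-FSDS as an objective.

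For the efficacy analysis, section 2.10 plans a two-way ANOVA to "compare the changes in scores of each outcome for 8 weeks between the intervention groups or the facial shape types". The significance criterion is that a P "value < .05 will be considered statistically significant". Neither the word interaction nor an equivalent contrast appears in the article.

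Only the Discussion says what result would support the device. The condition reads: "If the symptoms of FD in this trial more significantly improve patients classified using the 3-FSDS as the bladder than the gallbladder body". If it is met, the authors conclude that the device is fit for sorting patients by type. Neither the condition nor that conclusion mentions the placebo group.

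Section 2.9 sizes the trial for the overall YGJT-placebo difference only.

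**The concern.** A difference in treatment effect between types is the quantity (YGJT minus placebo in bladder) minus (YGJT minus placebo in gallbladder). Section 2.10 names a comparison between intervention groups or between types, which describes the two main effects. The Discussion criterion is about how much each type improves.

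These are different quantities. Randomisation in section 2.4 is within type, and type itself is only observed. The types may differ in natural course, regression to the mean (entry requires a VAS above 40) or placebo response. Any such difference shifts both arms of one type together. It moves the type comparison but cancels out of the interaction.

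At stake are the claim that the device is useful and the expectation, also in the Discussion, that the trial will give evidence for prescribing YGJT by facial type.

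**Working it through.** **Inputs from the protocol.** Effect 1.57 TDS points, SD 2.148, allocation 2:1, two-sided 5% level, 80% power, 30% dropout (2.9); 48 patients per type (2.1). Per type this gives 32 YGJT and 16 placebo if all 96 are evaluable, or 22 and 11 if 66 are.

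**Input that is an assumption.** A gap b by which bladder patients improve more than gallbladder patients in both arms, whatever the treatment. The documents give no figure, so b = 0, 0.5, 1.0 and 1.57 are shown.

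**The plan's own figure.** n_c = (1 + 1/2) × [2.148 × (1.960 + 0.842) / 1.57]² = 22.04, total 66.1. The stated 22 + 44 = 66 reproduces, with power 79.9%. 66 / 0.70 = 94.3, so 96 is consistent with the 2:1 layout. This covers the overall YGJT-placebo comparison.

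**Standard errors for the type questions** (n_t and n_c per type, cells equally weighted):
- Interaction: SE = 2.148 × √[2(1/n_t + 1/n_c)]. At 22/11 this is 1.122; at 32/16 it is 0.930.
- Type main effect: half of that, 0.561 and 0.465.
- Type comparison within the YGJT arm: 2.148 × √(2/n_t) = 0.648 and 0.537.

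**Chance of a significant result when the YGJT effect is the same in both types** (two-sided 5%, noncentral t with N − 4 degrees of freedom):

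| Assumed gap b | Type main effect, N=66 | Type main effect, N=96 | Interaction |
|---|---|---|---|
| 0 | 5% | 5% | 5% |
| 0.5 | 14% | 19% | 5% |
| 1.0 | 42% | 57% | 5% |
| 1.57 | 79% | 92% | 5% |

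For example, at b = 1.0 and N = 96 the noncentrality is 1.0 / 0.465 = 2.15. Simulation of the two-way layout (20,000 runs per setting) agrees, and the rates are the same within simulation error whether YGJT has no effect in either type or a 1.57-point effect in both.

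Reading the Discussion criterion as a comparison of types among YGJT patients only does not remove the problem: at b = 1.0 the rate is 33% (N=66) to 45% (N=96).

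**What the interaction test can deliver.** For a true interaction of 1.57 points, the noncentrality is 1.57 / 1.122 = 1.40 at N = 66 and 1.57 / 0.930 = 1.69 at N = 96, giving power of about 28% and 39%. The interaction detectable with 80% power is (1.960 + 0.842) × SE, or 3.14 points at 66 and 2.61 at 96. Detecting 1.57 points would need about 265 evaluable patients.

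**The case against.** The strongest reply is that a two-way ANOVA with treatment and type as factors can contain the interaction, and nothing in 2.10 excludes it. A reader might infer that the plan has ruled the interaction out and will test main effects only. The text does not support that. The sentence is compressed, and the authors may intend the interaction. The Abstract sentence states the right target and needs no correction; in a placebo-controlled trial, treatment effect naturally means YGJT against placebo. What stands is narrower: the interaction is not named as the test that decides, and the only criterion written down is a different one.

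A reader might also take the Discussion's wording about improving more significantly to mean that P values will be compared across types. No section plans that, so no error rate for such a procedure is counted here.

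It is also fair to say that the type main effect holds 5% for its own null hypothesis, that inflation needs a real gap between types, and that a 1.57-point gap is as large as the whole assumed drug effect. All three points stand. But the design cannot exclude a gap, because type is not randomised, and even 0.5 points raises the rate to 14-19%.

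Finally, the criterion is Discussion text, and an article leaves detail to the full protocol. That would excuse an omission. It does not excuse a stated criterion that fails to match the stated aim.

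**Conclusion.** The point holds in this form. The aim is a difference in YGJT effect by facial type, 2.10 does not make the interaction the deciding test, and the Discussion criterion ignores placebo. Followed as written, that criterion can support the 3-FSDS when the YGJT effect does not differ by type. The risk is 5% with no gap between types and reaches 42-57% at an assumed gap of 1.0 point. These figures rest on SD 2.148, equally weighted cells and an assumed gap common to both arms; the documents neither give nor exclude such a gap. The overall YGJT-placebo comparison, the only one the sample size covers, is unaffected.

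**What to change.** In 2.10, state that the facial-type question is tested by the treatment × facial-type interaction in the already planned two-way ANOVA of change in TDS at week 8. Report it as the difference between types in (YGJT minus placebo) with a 95% CI. State that neither the type main effect nor improvement within a type will support the device claim. Reword the Discussion criterion to match.

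Label the question exploratory, given the low power, and state that a non-significant interaction will not be read as absence of a difference. Adjustment for age and sex is optional; with 11 to 16 placebo patients per type, there is little room for further terms.

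The change is to wording: no new data, visits or patients. The price is a wider interval (at N = 96 a half-width of about 1.99 × 0.930 = 1.85 points, against 1.99 × 0.465 = 0.92 for the type main effect) and a less favourable device claim.

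### Section 2.10 does not say which contrast decides the trial, although three different results each carry a positive conclusion and only pooled YGJT versus placebo was sized

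*Protocol article*

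**What the plan says.** Section 2.7.1 names one primary outcome, the TDS scale, and section 2.10 bases the primary analysis on the ITT set. For efficacy, section 2.10 gives a single method, a two-way ANOVA to "compare the changes in scores of each outcome for 8 weeks between the intervention groups or the facial shape types". The decision rule for all tests is that a P "value < .05 will be considered statistically significant". No contrast is called primary, and there is no order or division of alpha.

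Section 2.9 sizes one contrast only, treatment versus control on the TDS scale with the types pooled: 44 versus 22 evaluable subjects, raised to 96 for dropout. Section 2.1 splits the 96 into 48 bladder and 48 gallbladder subjects.

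Positive conclusions are attached to three different results:

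- **Pooled efficacy.** The abstract expects the trial to "provide objective evidence for prescribing the YGJT to FD patients in clinical practice".
- **Efficacy in one type.** The discussion begins a conclusion for practice with "If the efficacy of YGJT on FD patients classified as specific type is proven in this trial" and goes on to prescribing by facial type.
- **A difference between types.** The discussion treats greater improvement in the bladder type as showing that the 3-FSDS can be used for classification.

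**The concern.** A trial keeps its 5% error rate only if one result, fixed beforehand, decides it. Here a significant pooled effect, a significant effect in one type, or a significant difference between types could each be presented as the trial succeeding, all at the same threshold. If YGJT does nothing in either type, there are several chances to report otherwise.

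The second and third conclusions are those that would change prescribing by facial type and support the device. Neither was sized, so the plan as written would let an unpowered contrast be described as proven.

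**Working it through.** **Inputs.** From section 2.9: difference 1.57, SD 2.148, power 80%, alpha 5% (two-sided, since the formula uses Z at α/2), ratio 2:1, dropout 30%. From section 2.1: 48 subjects per type with the same 2:1 ratio in each, so 32 YGJT and 16 placebo per type.

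**1. The plan's own figure.** n_c = (1.960 + 0.842)² × 2.148² × (3/2) / 1.57² = 22.04 and n_t = 44.08, stated as 22 and 44. Power at 44 versus 22 is 79.9%. Then 66 / 0.7 = 94.3, rounded up to 95; 96 gives two equal types at 2:1. The figure reproduces, and it is for the pooled contrast alone.

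**2. How the tests relate.** Let Z_B and Z_G be the standardised YGJT–placebo differences in the two types. They come from different subjects, so they are independent. With equal type sizes and ratios:

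- pooled effect = (Z_B + Z_G)/√2
- treatment-by-type interaction = (Z_B − Z_G)/√2

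These two are uncorrelated. A standard two-way ANOVA gives both, although section 2.10 does not name the interaction. The two within-type tests are Z_B and Z_G themselves. They are not listed in section 2.10 and are inferred from the discussion.

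**3. Chance of at least one two-sided P<.05 with no effect anywhere.**

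- Pooled plus interaction: 1 − 0.95² = 9.75%.
- All four tests: non-significance on all four means that (Z_B, Z_G) lies inside a regular octagon at distance c = 1.96 from the origin. The probability of falling outside is (8/π) ∫₀^{π/8} exp(−c²/(2cos²θ)) dθ. Simpson's rule with three points gives (0.1465 + 4 × 0.1358 + 0.1054)/6 = 13.25%. Simulation with 20 million draws also gave 13.25%, and t-tests with cells of 32/16/32/16 gave 13.3%.

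**4. Counting only results in the expected direction** (YGJT better; larger effect in the bladder type). One test: 2.5%.

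- Pooled plus interaction: 1 − 0.975² = 4.9%.
- All four: 7.5% by simulation (9.1% if an interaction in either direction counts).

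**5. Power of the unsized contrasts**, with the same 1.57 and 2.148 and a normal approximation.

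| Contrast | 96 analysed | 66 analysed |
|---|---|---|
| Within one type | 66.5% (32 v 16) | 50.8% (22 v 11) |
| Interaction of 1.57 points | 39% | 29% |

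For the within-type test at 32 versus 16: SE = 2.148 × √(1/32 + 1/16) = 0.658; 1.57/0.658 − 1.96 = 0.43, giving 66.5%. For the interaction at 96: SE = 2.148 × √(2 × (1/32 + 1/16)) = 0.930; 1.57/0.930 − 1.96 = −0.27, giving 39%.

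The ANOVA also tests a main effect of facial type. It is left out because it says nothing about YGJT against placebo. Adding it would give 14.2% for the three ANOVA tests and 17.6% for all five.

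**The case against.** The best defence is that the primary contrast can be worked out: one primary outcome, one sized comparison, ITT as the primary set. Read that way, the primary error rate is 5% and the rest is secondary. An article may also leave test order to the full protocol or SAP. That explains a missing hierarchy. It does not remove the difficulty, because this text itself fixes P<.05 for every test and ties separate conclusions to separate contrasts. The sizing does support the choice of primary contrast proposed below.

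Three stronger readings are tempting and should be resisted.

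- **That the chance of a false positive claim is 13% instead of 5%.** The 13% counts placebo beating YGJT and gallbladder beating bladder, neither of which supports the claims made. It also needs within-type tests that section 2.10 does not list; the discussion wording could describe a treatment-by-type result.
- **That week 4 opens further routes.** Section 2.7.1 says "This scale will be assessed at baseline, 4 weeks, and 8 weeks", but section 2.10 specifies change over 8 weeks. Measuring at week 4 does not make it a second success criterion, and any figure would need a correlation between visits that the document does not give.
- **That the interaction must be tested only after a significant pooled result.** The type comparison is the study's stated novelty, so this is a real trade-off. If the 1.57-point effect existed only in the bladder type (an assumption), pooled and interaction tests would each have about 39% power with 96 subjects, and requiring both leaves 0.39 × 0.39 ≈ 15%. The documents do not settle that choice.

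**Conclusion.** The point holds as a rule that is fixed badly: one threshold for every contrast, three results with a positive conclusion attached, no statement of which decides, and a sample size for only one of them. The inflation is moderate. On the tests that a two-way ANOVA supplies, the error is about 9.7% against 5% two-sided, or about 5% against 2.5% in the expected direction. With the inferred within-type tests it is about 13%, or about 7.5% in the expected direction.

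These figures assume no effect in either type, the full 32/16 split per type, one outcome at one time point, and one analysis set. The change should be made, since it is cheap and follows the contrast that the trial was built for.

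**What to change.** Add to section 2.10:

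- The single primary contrast is the YGJT-minus-placebo difference in TDS change from baseline to week 8, both facial types pooled, in the ITT set, at two-sided 5%.
- The treatment-by-type interaction on the same outcome is a secondary test. Any type-specific or 3-FSDS conclusion must rest on it, and it is described as supportive and not powered.
- Within-type differences and week-4 differences are reported as estimates with 95% CIs, without significance claims.

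The discussion should use the same terms, so that efficacy in a specific type is not described as something this trial can prove. The cost is a few sentences, with no extra subjects, visits or data. The small downside is that a result seen in one type only cannot be claimed as proven.
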